#### Other outcomes

Information on the child’s glycemic control (HbA1c) and the number of hospital admissions of 24 hours or over in case of keto-acidosis or severe hypoglycemia, throughout the entire study-period are derived from the child’s medical files (see Table 5).

**Table 5 T5:** Other measures used in the Sugarsquare study

**Outcome**	**Measures**
Medical parameters	• HbA1c
	• Hospitals admissions due to glycemic disruptions

### Analyses

#### Descriptive statistics

Demographics of the research sample will be analyzed descriptively. Secondly, differences at baseline between subpopulations and clinics will be assessed by using analysis of variance (ANOVA).

#### Primary analysis

To compare differences between treatment and control group on our primary outcome measure on T0 and T1, analyses of covariance (ANCOVA) will be performed on T1 data, using T0 data as covariates. Effects for clinic differences will be taken into account. A sensitivity analysis will be conducted by means of a multiple imputation analysis (based, among others on HbA1c scores of the population at T1) and an analysis based on a Last Observation Carried Forward (LOCF) imputation.

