#### Procedures

Eligible, potential participants are approached by their diabetes care team with hard-copy information (information letter, flyer, brochure and application form) about the study. Upon returning the application form, participants are randomized and are subsequently send a questionnaire. When participants have sent back their filled out baseline questionnaire, they are informed about the allocation. Participants who fail to return their baseline questionnaire are contacted by telephone by their diabetes care team, requesting them to send back the filled out questionnaire. After six months following baseline assessment, a second assessment is conducted, also by means of a questionnaire. After having sent back the second questionnaire, participants in the experimental group retain access. Participants in the control group are granted access after having sent back their second questionnaire. After twelve months following baseline assessment, a third assessment will take place, again by means of a questionnaire. Participants who fail to return their second or third questionnaire after request over telephone are considered as drop-out.

All procedures described in this study protocol are approved by the Ethics Committees of Human Experimentation of the Radboud university medical center and of the participating hospitals and are in accordance with the Declaration of Helsinki. Written informed consent will be obtained from all participants.

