### Sample size

We aim to include 240 parents. This number of participants is calculated using a medium effect size (d = .5), an α of .05 (two-tailed test) and a β of .10. The hypothesized effect size is realistic, when considering the paper of Leung et al. ([38]; see also Table 1), in which an effect size of 1.38 was described, using the PSI-SF. To reach adequate power (.90), 180 participants are included in the final analysis [39]. These participants are divided equally into an experimental group (N = 90) and a control group (N = 90). However, in recent studies on randomized controlled trials regarding E-health interventions, an average dropout rate of 25% was found [28]. This means that, when taking drop-out into account and when aiming at 180 participants in the final analyses, at least 240 parents have to be included at the start of the study.

**Table 1 T1:** **Means and standard deviations of the parent-reported measures of the PSI**[38]

**Intervention group**		**Control group**	
**M(SD)**		**M (SD)**	
Pre intervention	Post intervention	Pre intervention	Post intervention
121.60 (17.16)	85.27 (19.91)	112.87 (14.35)	109.08 (14.98)

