### Data-collection

Data are collected through self-report questionnaires except for the medical data and user statistics. All questionnaires are sent at baseline, T1 (6 months following baseline) and T2 (12 months following baseline), through the internet. All data are collected using Radquest. Radquest is software used for composing and storing questionnaires using a secured server and was developed by the department of Medical Psychology of the Radboud university medical center. Data derived from patients’ medical files are gathered by nurse practitioners of the diabetes care teams.

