Sugarsquare provides patients and healthcare professionals with an innovative and easy-accessible tool. Sugarsquare is expected to support parents in coping with and learning about diabetes through exchange of experiences and ideas with peers and to ease communication between parents and healthcare professionals. It is also expected to be feasible as it contributes to the multidisciplinary character of diabetes care by making all communication between healthcare professionals and parents visible for and accessible to all involved healthcare professionals. Combining those aspects in one intervention is an important strength of our study. A second strength of this study is that it incorporates patient participation in the development of the intervention. By exploring needs and wishes of the users and by extensive piloting of the intervention, we were able to fine-tune the intervention to users’ preferences [17,52]. This will contribute to usability of the intervention and to its generalizability when implementing the intervention in daily care. A third strength of this study is the design of the feasibility assessment using domains proposed by Bowen [51]. This design will enable us to link usage of different sections or applications in the intervention to change in different domains. This design is, on the other hand, also a vulnerability. A design using one arm for every section or application would make it easier to assess the separate contribution of individual sections or applications. However, a web-based patient portal such as Sugarsquare highly depends on the number of users [31]. In the Netherlands, Diabetes care is organized locally, resulting in a great number of diabetes teams with relatively small populations. To get enough users in the intervention group, we could only take on two arms in the present study: 1) an experimental arm and 2) a control arm. Another vulnerability is the chance for drop-out. Studies on internet-delivered interventions often suffer from high drop-out rates, which can significantly interfere with finding potential efficacy of the intervention [28]. To minimize interference, we took a drop-out rate of 25% into account in the sample size calculation. However, we can still be confronted with problems regarding power in the intention-to-treat analysis.

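### At T1 the planned LOCF sensitivity analysis is baseline carried forward: it dilutes a true effect, and it biases the comparison if unequal drop-out meets a time trend

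*Protocol article*

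**What the plan says.** The Primary analysis section compares the arms at six months: "analyses of covariance (ANCOVA) will be performed on T1 data, using T0 data as covariates". It then names two sensitivity analyses. One is a "multiple imputation analysis (based, among others on HbA1c scores of the population at T1"); the other is "an analysis based on a Last Observation Carried Forward (LOCF) imputation".

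The Data-collection section sets the timing: "All questionnaires are sent at baseline, T1 (6 months following baseline) and T2 (12 months following baseline"). T0 is therefore the only questionnaire before T1.

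The Sample size section plans on "a medium effect size (d = .5), an α of .05 (two-tailed test) and a β of .10", with 180 parents analysed. It raises this to 240 because, in other e-health trials, "an average dropout rate of 25% was found". It gives no split by arm. The Procedures section says "Participants in the control group are granted access after having sent back their second questionnaire". The Discussion names drop-out as a vulnerability and warns that "we can still be confronted with problems regarding power in the intention-to-treat analysis".

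**The concern.** A sensitivity analysis is useful when it changes the missing-data assumption in a way the reader can interpret. With a single earlier score, LOCF assumes that every parent without T1 stayed exactly at baseline, in both arms, whatever happened to the other parents in that arm. That penalises drop-outs by an amount the analyst does not choose: it is set by the size of the effect and by any general drift in stress over six months.

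Two consequences follow. A true effect is diluted roughly in proportion to drop-out in the intervention arm. And if the arms lose different shares of parents while stress drifts in both, the arm with more carried-forward scores shows less of the drift, which creates a difference that is not a treatment effect. If LOCF then disagreed with multiple imputation, the reader could not tell whether the cause was the intervention, the drift or the pattern of loss.

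**Working it through.** **The plan's own figure.** 180 / (1 − 0.25) = 240, as stated. A quarter of 240 is 60 parents, or 30 per arm if loss is equal.

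**Expected LOCF estimate.** Work in SD units, with lower stress counted as benefit. Let *e* be the true effect, *t* a fall common to both arms, and *p*I and *p*C the shares without T1 in the intervention and control arms. Assume loss is random within arm and drop-outs would have had the same effect and fall as completers. Carried-forward parents contribute zero change, so

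LOCF difference = (1 − *p*I)(*e* + *t*) − (1 − *p*C)*t* = (1 − *p*I)*e* − (*p*I − *p*C)*t*.

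**Inputs.** From the protocol: *e* = 0.50, 240 enrolled (120 per arm), 25% overall drop-out. Table 1 shows the cited study's controls moving from 112.87 (SD 14.35) to 109.08, so 3.79 / 14.35 = 0.26 SD; I use this as an illustrative *t*. Not in the protocol, and assumed here: the split of drop-out by arm, a T0–T1 correlation of 0.5 or 0.7, and 0.5 SD as a larger trend.

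**By formula:**
- 25/25, any *t*: 0.75 × 0.50 = 0.375.
- 35/15, *t* = 0: 0.65 × 0.50 = 0.325.
- 35/15, *t* = 0.26: 0.325 − 0.20 × 0.26 = 0.273.
- No effect, 35/15, *t* = 0.26: −0.20 × 0.26 = −0.052, in the direction of harm.
- No effect, 15/35, *t* = 0.26: +0.052, in favour of the intervention.

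**By simulation.** ANCOVA of T1 on arm and T0, 120 per arm, 6,000 trials per row. Ranges cover the two correlations; drop-out is intervention/control.

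| True d | Fall (SD) | Drop-out % | LOCF estimate | LOCF rejection | Completer rejection |
|---|---|---|---|---|---|
| 0.5 | 0 | 25/25 | 0.372–0.374 | 0.953–0.996 | 0.969–0.996 |
| 0.5 | 0 | 35/15 | 0.323–0.327 | 0.885–0.974 | 0.966–0.995 |
| 0.5 | 0.26 | 35/15 | 0.273–0.274 | 0.722–0.870 | 0.968–0.993 |
| 0 | 0.26 | 25/25 | about 0 | 0.046–0.050 | 0.050 |
| 0 | 0 | 35/15 | about 0 | 0.052–0.054 | 0.049–0.050 |
| 0 | 0.26 | 30/20 | −0.023 to −0.028 | 0.057–0.060 | 0.047–0.050 |
| 0 | 0.26 | 35/15 | −0.052 | 0.083–0.098 | 0.048–0.051 |
| 0 | 0.26 | 40/10 | −0.074 to −0.077 | 0.116–0.150 | 0.048–0.053 |
| 0 | 0.5 | 35/15 | −0.099 to −0.100 | 0.148–0.214 | 0.048–0.051 |
| 0 | 0.26 | 15/35 | +0.050 to +0.052 | 0.077–0.102 | 0.049–0.050 |

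Formula and simulation agree.

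**Direction.** In a separate run with correlation 0.6, no effect, 35/15 drop-out and a 0.3 SD fall (4,000 trials), 0.5% of trials rejected in favour of the portal and 9.6% in the direction of harm.

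**The implied penalty.** With *e* = 0.50 and *t* = 0.26, LOCF moves intervention drop-outs by 0.50 + 0.26 = 0.76 SD and control drop-outs by 0.26 SD, relative to what they would have scored on average. At 35/15: 0.50 − 0.35 × 0.76 + 0.15 × 0.26 = 0.273, as above.

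**The case against.** The strongest defence is that LOCF may be a reasonable pessimistic scenario here. If intervention parents who drop out gain nothing and there is no time trend, the true intention-to-treat effect at 25/25 is 0.75 × 0.50 = 0.375. LOCF returns that value, while the completer analysis returns 0.50. So 0.37 is a dilution only if drop-outs share the effect. This stands. It also means a reader should not infer that the plan contains no analysis under non-random drop-out: LOCF is one such assumption, fixed and crude. What is not described is any analysis that varies it. In a condensed article, with the analysis plan not shown, that absence alone would not be a finding; the point rests on the method that is stated.

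A reader might also infer that unequal drop-out by itself inflates type I error. It does not: at 35/15 without a trend, rejection is 5.2 to 5.4%. Nor did carrying scores forward inflate error when loss was equal (4.6 to 5.0%), so an argument from understated residual variance has no shown consequence.

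The case for unequal drop-out is only moderate. Controls gain access by returning the T1 questionnaire, which rewards return in that arm. But the Procedures section also has the experimental group keeping access after returning it, which can be read as a similar link, and the telephone request is not limited to one arm. Finally, 25% is a planning average, and the protocol counts a missing T1 or T2 as drop-out, so fewer than a quarter may lack T1.

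**Conclusion.** The point holds in a limited form. For the T1 outcome, LOCF is baseline carried forward. If drop-outs would have had the same effect as completers, it shrinks d from 0.50 to about 0.37 at 25% loss per arm. If loss also differs by arm and stress falls in both, it is biased: at an assumed 35/15 split and 0.26 SD fall, type I error is about 8 to 10%, mostly towards false harm, and power drops to 0.72–0.87 against 0.97–0.99 in completers. At 30/20 type I error is about 6%. Only the reverse split would push towards false benefit.

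These sizes rest on an assumed split, correlation and trend, and on loss at random within arm. It would be tempting to conclude that the trial's main result is at risk. The protocol does not support that: LOCF is one of two sensitivity analyses, multiple imputation is also planned, and the primary ANCOVA does not use LOCF. The defect is a stated robustness check whose agreement or disagreement with the main result would be hard to interpret. It is worth correcting but does not threaten the design.

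**What to change.** Replace LOCF with a delta-adjusted or tipping-point version of the multiple imputation already planned. Impute T1 by arm, then make the imputed scores of intervention drop-outs progressively worse, and report the shift at which the conclusion changes. That range states its assumption openly and covers the worry that parents who leave do worse than predicted. If LOCF is kept, label it as a scenario of no change from baseline and do not treat it as a general check of robustness. Because the Secondary analysis section calls for similar analyses, the same wording should apply wherever LOCF would be used there. The choice of imputation variables can stay with the analysis plan.

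The cost is a sentence or two of revised text and a small amount of extra programming. No new data are needed.

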#### Secondary analysis

Similar analyses are conducted for exploring effects on secondary outcome measures and medical parameters. Data on T2 is regarded as follow-up.

#### Feasibility

For feasibility, user data will be explored, by means of descriptive statistics. Association of user data with individual characteristics on baseline, change on primary and secondary outcome measures and medical parameters will be explored, using Pearson Correlations Coefficients and univariate ANOVA.

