## Methods/Design

### Setting and participants

The present study is conducted in seven clinics for pediatric diabetes care in the Netherlands which, together, deliver care to approximately 750 children with diabetes under the age of 13. Eligible participants are parents of a child with T1D, who receives treatment at one of the seven clinics for diabetes care. Parents are excluded when their child reaches the age of 13 before start of the study. No access to the internet at home and limited comprehension of the Dutch language are also reasons for exclusion.

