#### Intervention

The final version of Sugarsquare consists of a web-based patient portal which provides disease information, easily accessible contact with the diabetes care team and peer support. In accordance to parents’ preferences, the intervention is organized locally. This means that every clinic has its own secured portal, which is only accessible to healthcare professionals of that particular clinic and parents of children treated at that clinic. Sugarsquare is accessible through the internet and consists of three main sections:

Section I: Social

This first section includes online peer support and is accessible to all users (parents and healthcare professionals). Peer support is facilitated through a chat-application, a forum-application and a blog-application. Parents and healthcare professionals are able to communicate in real time by using the chat-application. On the forum-application, healthcare professionals and parents can read and post messages, which are open to all users. Since all users contribute to the social section, it will grow out to have great educational value.

Section II: Personal

This second section applies to individual patients and the information exchanged there can therefore only be accessed by the parents of that particular patient and all healthcare professionals of the clinic. The section consists of an application for overview of treatment goals and an application for easy accessible private contact with the healthcare professionals. The treatment goals are composed during regular consultations with the nurse practitioner and can be accessed online by parents and healthcare professionals at any given moment. The application for easy accessible communication with healthcare professionals is used by parents for discussing the child’s treatment and wellbeing. Discussions are accessible to both parents and all professionals of the diabetes care team. This allows healthcare professionals to fine-tune their advice to previously given advices. This application is only used for non-urgent matters.

Section III: Information

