The third section contains disease information, which is presented by means of downloadable documents and web links. Each diabetes care team prepares documents and selects web links. Parents can add web links to Sugarsquare as well, which the diabetes care team can choose to endorse after review. All posted information in this section is available to all users. A screenshot of the login page of Sugarsquare is presented in Figure 1.

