### Study design and procedure

#### Design

A 12-month, multicenter, randomized controlled trial (RCT) is conducted, in which participants are assigned to one of two conditions: 1) an intervention condition and 2) a waiting-list control condition. Participants in the intervention group have access to the intervention during the entire 12-month study period. Participants in the control group are placed on a six-month waiting list. In the remaining six months they will have access to Sugarsquare.

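### The exploratory portal-use associations name no clinic term, although each clinic runs its own portal; a clinic difference could then look like a parent characteristic linked to use

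*Protocol article*

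**What the plan says.** The Feasibility paragraph under Analyses plans two things: a descriptive account of the user data, then an exploration of what use is related to. The second part reads "Association of user data with individual characteristics on baseline, change on primary and secondary outcome measures", and goes on to say that these and "medical parameters will be explored, using Pearson Correlations Coefficients and univariate ANOVA". It mentions neither clinic, arm nor length of access.

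Other parts of the protocol article bear on this:

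- **Setting and participants:** "The present study is conducted in seven clinics for pediatric diabetes care in the Netherlands".
- **Intervention:** "every clinic has its own secured portal, which is only accessible to healthcare professionals of that particular clinic" and to the parents of children treated there. On content, "Each diabetes care team prepares documents and selects web links".
- **Discussion:** the authors acknowledge that a portal of this kind depends strongly on how many people use it, and that local populations are fairly small.
- **Primary analysis:** for parenting stress, "Effects for clinic differences will be taken into account".
- **Descriptive statistics:** baseline differences between clinics will be examined.
- **Design:** the intervention arm has access for 12 months. "Participants in the control group are placed on a six-month waiting list" and have access for the remaining six.
- **Randomization & blinding:** allocation is done per centre, with equal numbers of cards for the two arms.

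**The concern.** Logins and forum posts partly measure the parent and partly measure the portal the parent was given. A parent attached to a lively local forum has more reason to log in than the same parent attached to a quiet one. A Pearson coefficient across all parents cannot separate the two sources.

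Suppose one clinic has a busy portal and also treats more children by pump. Pump treatment would then correlate with use across the whole sample, even if pump and pen families within each clinic used the portal equally. The report would describe a type of parent when the finding was about a clinic. The protocol recognises clinic as a source of variation for the stress outcome but names no clinic term for use, although the intervention itself is delivered clinic by clinic.

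At stake is the description of which parents use the portal. The efficacy result is not affected.

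**Working it through.** The plan states no error rate or power for these associations, so there is no figure of its own to reproduce. Its total of 240 parents, used below, does reproduce: 180 / (1 − 0.25) = 240 (Sample size).

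**Inputs from the document:** N = 240; 7 clinics; 1:1 allocation within centre; 12 against 6 months of access.

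**Assumptions, because the document gives no values:** the intraclass correlation (ICC) by clinic of use (ρu) and of the characteristic (ρx), clinics of equal size, a nominal two-sided 5% test, and no true link between use and the characteristic within clinics.

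**Step 1: approximation.** With m = N/7 parents per clinic and independent clinic effects, the variance of the correlation is multiplied by about

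f = 1 + (m − 1) × ρu × ρx,

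and the actual false-positive rate is about 2 × [1 − Φ(1.96 / √f)].

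Here m = 240/7 = 34.3. With both ICCs at 0.10, f = 1 + 33.3 × 0.01 = 1.333, √f = 1.154 and 1.96/1.154 = 1.698, which gives 9.0%. The ICCs enter as a product, so if either is zero, f = 1 and the rate stays at 5%.

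**Step 2: simulation** (3,000 runs unadjusted, 1,500 with clinic means removed).

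| ρu / ρx | f | Formula | Simulated, unadjusted | Simulated, within clinic |
|---|---|---|---|---|
| 0 / 0 | 1.000 | 5.0% | 4.5% | 5.0% |
| 0.10 / 0 | 1.000 | 5.0% | 5.6% | 5.0% |
| 0.05 / 0.05 | 1.083 | 6.0% | 5.9% | 4.5% |
| 0.10 / 0.10 | 1.333 | 9.0% | 9.3% | 5.8% |
| 0.20 / 0.10 | 1.666 | 12.9% | 10.7% | 3.8% |
| 0.30 / 0.10 | 1.999 | 16.6% | 14.7% | 5.0% |
| 0.20 / 0.20 | 2.331 | 19.9% | 16.3% | 4.5% |

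The formula runs above the simulation at high ICCs because it ignores that there are only seven clinics. The 5.6% in the second row is within simulation error of 5%: the standard error is √(0.05 × 0.95 / 3000) = 0.4 points.

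**Step 3: count data.** A second simulation (1,500 runs per setting) used skewed login counts, clinics of unequal size and 12 against 6 months of access. The clinic SD of log use was set at 0.5 to 1.0 and the characteristic's ICC at 0.05 to 0.20. The pooled Pearson test gave 6% to 18%. A model of log use per month with clinic and arm gave about 4% to 7%. For example, at SD 0.7 and ICC 0.10 the rates were 9.3% and 6.5%; at SD 1.0 and ICC 0.20 they were 17.5% and 4.2%.

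**Step 4: one arm only.** With N = 120, the unadjusted rate was 4.3% to 11.3% over the same ICC settings as in Step 2. The problem is smaller but does not depend on pooling the arms.

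**Step 5: access time.** With arms pooled, raw counts and an assumed 2 logins per month, the false-positive rate against a baseline characteristic was 4.8% on raw counts and 5.6% per month of access, so there is no inflation. The cost is precision. With a true rate ratio of 1.25 to 1.28 per SD and no clinic effects, power was 0.60 to 0.77 on raw counts and 0.66 to 0.85 on use per month.

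**The case against.** The other side has four fair arguments.

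- **Clinic variation is assumed.** Table 2 only lists the baseline variables, and the Descriptive statistics paragraph says differences will be examined, not that they exist. The Diabetes team section gives nurse practitioners the same portal tasks in every clinic, which would narrow differences in use. This stands. Separate portals and local content make variation in use plausible, but its size is unknown, and variation in parent characteristics is a further assumption.
- **The wording may leave room for clinic.** A univariate ANOVA has one dependent variable and may still carry several factors. This stands in part: a clinic factor is possible there but is not named, and a Pearson coefficient cannot carry one.
- **Arm, time window and scale of use are not stated.** An article may leave them to the full protocol. This stands. Pooled arms and raw counts are inferences, and the clinic point does not need them.
- **The analysis is exploratory.** No significance level or decision rule is attached to it. This stands and keeps the severity low, but confounding by clinic affects an exploratory estimate as well.

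A reader might also infer that the 12- against 6-month difference in access could pass for a parent characteristic. The documents do not support that. Access length is the randomised arm, allocated with equal numbers of cards within each centre, so it has no systematic link to baseline characteristics. Relating use to outcome change is a separate matter, because there access length coincides with the treatment contrast; it is not part of this point.

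**Conclusion.** The point holds for clinic and for associations of use with baseline characteristics. The plan names bivariate or single-outcome tests with no clinic term for a measure that is generated clinic by clinic, while it allows for clinic in the primary analysis. If both use and the characteristic vary by clinic, false positives are roughly 6% to 18% at a nominal 5%, and higher with stronger clustering. At an ICC of 0.05 for both, the excess is only about one percentage point. If only use varies, there is little or no inflation. All these rates rest on assumed clinic variation and on a 5% level that the plan does not itself attach to these tests.

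A reader might infer that such associations would decide how the portal is implemented. The text does not go that far: implementation is tied to efficacy and feasibility, and Table 4 defines feasibility by percentages of users, inventories, duration of use and a guideline evaluation. This is a cheap improvement to an exploratory analysis, of low severity. The primary ANCOVA is untouched.

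**What to change.** In the Feasibility paragraph under Analyses, replace the unadjusted correlation and ANOVA for use by a regression of use on the characteristic, with clinic as a term, and arm as well if both arms are used. Express use per month of access, either by a count model with log months of access as offset or as log use per month. State which arm and time window the user data come from. Report the within-clinic associations, labelled exploratory, and describe differences in use between clinics separately.

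The change takes about one sentence and needs no new data. It adds six parameters for seven clinics (7 − 1) and one for arm, and the resulting statistic is slightly less familiar than a correlation coefficient.
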